### **4.3 Exclusion criteria**

- Patients with metal implants in the pelvic area
- Patients with a pacemaker

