### Primary Objective:

Feasibility and safety of an in-house developed electromagnetic navigation system during abdominal surgery.

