### **4.2 Inclusion criteria**

- Patients who are scheduled for abdominal surgery
- Locally advanced T3 or T4 tumour or local recurrent tumour
- Patients should be suitable for contrast enhanced CT scanning
- A signed informed consent
- Patients  $\geq 18$  years old

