#### In the OR:

- In the OR the patient will be placed on the table according to standard protocol, with the exception that the EM field generator will be placed between the table and the patient (Fig. 1).
- The marker-patches will be positioned at the scan locations and the navigation system will be calibrated.
- The 3D reconstructions will be loaded into the navigation software.
- An intra-operative XPerCT (no contrast fluid used) is acquired to assess the actual patch positions with respect to the 3D model. The XPerCT is used to improve the navigation accuracy.
- Before surgeons start applying the sterile field, an estimate of the registration accuracy between the CT and actual marker positions will be performed. If tolerance limits are exceeded, the navigation procedure during surgery will be cancelled.
- At the moment the laparotomy is advanced to the stage in which the iliac vessels are visible for the surgeon the study measurements are started.
- After the measurements the surgeon will proceed with the standard surgery. If the tumour is rigid, or pathologic lymph nodes are present around the large vessels, the navigation system can be used to localize them.

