## **5.2 Investigational products**

The navigation system used for this study is composed of elements of the Aurora Electromagnetic Measurement System from Northern Digital Inc. (Waterloo, Ontario, Canada) and is combined with in-house developed software for the navigation and visualisation. The system is developed for use in the NKI-AvL only, and there is no current intent to commercialize the system. According to Dutch national guidelines (beleidsplan medische apparatuur), and agreements between the METC and the department of clinical physics, a tailored safety management and risk assessment protocol should be followed which is adapted to the specific medical device.

For technical validation of the navigation system before start of the study we will provide:

- A risk assessment, in collaboration with [name] (Clinical physicist)
- A detailed description of the medical device and software, together with a report of pre-clinical tests on system accuracy, in collaboration with [name] (Clinical physicist)
- A report on electrical safety, in collaboration with [name] (Electrical safety officer)
- A safety protocol for sterile use of the probe and reference markers in collaboration with [name] (Sterile safety officer)
- A detailed operating manual for use in the OR, in collaboration with [name] (Teamleader OR)

After all protocols and manuals have been approved, approval of [name] (head of clinical physics department) will allow the use of the navigation system for the study.

The major risk domains for the current study are electrical safety, sterility, and unforeseen inaccuracies leading to misguidance of the surgeon.

The NDI Aurora hardware has been embedded in several commercial navigation systems, such as the Philips Percunav system. Electrical safety is extensively tested and described by NDI, and will be independently validated by [name].

Two components of the system will come in contact with the patient, being the reference patches and the blunt tip probe. The reference patches are developed by Philips in collaboration with NDI, and are provided in a sterile package. The blunt tip probe can withstand autoclave procedures, and will be tested on sterility by [name]. An alternative option is to use a sterile cover which is also used for hand-held ultrasound probes.

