#### Navigation hardware

The navigation system consists of several components, being 1) the EM field generator; 2) the blunt tip trackable probe; 3) the reference marker-patches; 4) the sensor interface units; 5) the system control unit.

[figure not shown]

Figure 1: Schematic side-view of a typical patient setup for pelvic cancer surgery, combined with the Aurora navigation system

[figure not shown]

Figure 2: Overview of the navigation hardware components and the interconnections between the components

A side-view of the patient setup in combination with the navigation system is shown in figure 1. A schematic overview of the navigation hardware and the interconnections is shown in figure 2. Of the system components, the blunt tip probe and reference patches will come in contact with the patient. Only the blunt tip probe (Fig. 3) will actually be used within the sterile surgical field.

The EM navigation system generates a known electromagnetic field. Small EM sensors which are located within the EM field will generate a current which can be measured through a sensor interface. Based on the current the exact location and orientation of the sensor within the EM field can be determined. The EM sensors are typically 1 mm in diameter and 8-10 mm long. Sensors can easily be embedded in surgical tools, such as a blunt tip probe, a laparoscopic camera, or a surgical knife.

The used EM field generator is a next generation tabletop version. This generator is placed underneath the patient, and has a shielding layer to minimize influence of metal in the table

to the accuracy of the magnetic field. Maier-Hein *et al.* have shown that this EM field generator has an accuracy in the order of 1mm within a clinical environment, which is suitable for our application.

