### **5.3 Use of co-intervention**

No specific restrictions for included patients are specified. Included patients will follow the same pre-operative workup as non-included patients scheduled for a similar operation.

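### Section 4.3 excludes pacemakers but no other active implant, so a patient with such a device outside the pelvis is eligible to lie over the electromagnetic field generator

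*Protocol*

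**What the plan says.** Protocol section 4.3 lists two exclusions: "Patients with metal implants in the pelvic area" and "Patients with a pacemaker". It gives a reason for neither.

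The inclusion criterion in section 4.2 that comes closest to an implant screen is "Patients should be suitable for contrast enhanced CT scanning", which concerns imaging.

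On exposure, section 5.1 (In the OR) states that "the EM field generator will be placed between the table and the patient". Section 5.2 (Navigation hardware) repeats this and describes the shielding: "This generator is placed underneath the patient, and has a shielding layer to minimize influence of metal in the table".

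On risk, section 5.2 states: "The major risk domains for the current study are electrical safety, sterility, and unforeseen inaccuracies leading to misguidance of the surgeon". The same section promises several documents before the study starts, among them a risk assessment, a device description, an electrical safety report and an operating manual. Use of the system depends on their approval.

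The primary objective in section 2 is "Feasibility and safety of an in-house developed electromagnetic navigation system during abdominal surgery".

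**The concern.** The pacemaker bullet protects against something, and the pelvic metal bullet suggests what. If the worry were distortion of the field by metal, the first bullet already deals with it, and the sponsor limited that bullet to the pelvis. A pacemaker normally lies outside the pelvis. Naming it separately makes sense mainly because it is an active electronic device near a field generator, and that description also fits other active implants. The criterion therefore looks narrower than its evident purpose.

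The study has few safeguards beyond eligibility. There is no data safety monitoring board (section 7.4) and no planned monitoring (section 6.5), and no serious adverse events are expected (section 7.2). Under sections 6.4 and 7.2, a serious event that could in any way be linked to the study is a ground for ending it. One such event in a patient with an implant could stop the study and would cloud its safety conclusion.

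**Working it through.** The plan gives no figure on this point, so there is none to reproduce. The main check is of the text.

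**Step 1: does any section stop the patient?** Take a patient aged 18 or over with a locally advanced tumour, scheduled for laparotomy, fit for contrast CT, consenting, and carrying a chest-wall defibrillator.

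| Section | What it screens | Stops this patient? |
|---|---|---|
| 4.2 Inclusion | Surgery, tumour stage or recurrence, CT suitability, consent, age | No |
| 4.3, first bullet | Metal in the pelvis | No, the device is in the chest |
| 4.3, second bullet | Pacemaker | No, not as worded |
| 5.2 Safety protocol | Registration error and probe pointing before surgery | No, it tests position accuracy only |
| 6.3 Withdrawal | Urgent medical reasons, or problems that prevent measurement | Not an implant screen |

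The patient is eligible. The same holds for a stimulator or pump sited outside the pelvis. It does not hold for a metal-containing device within the pelvis, which the first bullet excludes.

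**Step 2: is the patient exposed?** Yes. Sections 5.1 and 5.2 both put the generator under the patient. The stated purpose of the shielding is to limit the effect of metal in the table on accuracy. Protection of implants is not mentioned.

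**Step 3: how likely is such an enrolment?** The protocol gives no prevalence. Assume that a proportion p of eligible patients carries a non-pacemaker active implant outside the pelvis, with p = 0.5%, 1% or 2%. Section 4.4 adds 20 patients in the current extension. With n = 20:

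- chance of at least one carrier = 1 − (1 − p)^n
- expected number of carriers = n × p

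| p | Chance of at least one in 20 | Expected number in 20 |
|---|---|---|
| 0.5% | 1 − 0.995^20 = 0.10 | 0.1 |
| 1% | 1 − 0.99^20 = 0.18 | 0.2 |
| 2% | 1 − 0.98^20 = 0.33 | 0.4 |

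**Step 4: allowing for failures.** Section 4.4 plans for 30% failure. If all failures occurred before the patient lay on the generator, 20 × 0.7 = 14 patients would be exposed. The chances become 1 − 0.995^14 = 0.07, 1 − 0.99^14 = 0.13 and 1 − 0.98^14 = 0.25. This is a lower case, because some failures would occur after positioning.

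**The case against.** **The hazard is inferred.** The protocol gives no field strength, no rationale for the pacemaker exclusion, and no statement that the field affects any implant. A reader might infer that the protocol knowingly exposes patients to a documented danger, or that all active implants are equally susceptible. The documents support neither reading. What stands is that one active device is excluded without a reason and the others are not addressed.

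**Other documents may cover it.** The risk assessment, electrical safety report and operating manual in section 5.2 are conditions for using the system, and none is shown. The listed risk domains are only the major ones, and the scope of electrical safety is not defined. A reader might infer that nobody has considered other implants, which cannot be known from the protocol. Screening follows section 4.3, however. If those documents do exclude other active implants, section 4.3 fails to carry it.

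**Not every stimulator or pump is eligible.** A reader might take it that all of them are. The pelvic metal bullet rules that out.

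**Section 5.3 is weak evidence.** Its statement "No specific restrictions for included patients are specified" stands under co-intervention and concerns patients already included. It says nothing about eligibility, and the point does not rely on it.

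**The full sample of 95 is not the right base.** A reader might apply the formula in Step 3 to all 95 patients and get a much larger chance. That total includes patients already enrolled, whom a change now cannot affect.

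**Other protections exist.** The investigator may withdraw a patient for urgent medical reasons (section 6.3), and measurements take place under anaesthesia with physical monitoring (section 8.4). These mitigate the concern but do not replace a screen at entry. Any disturbance of the measurements by an implant is speculative and partly handled by the accuracy check in section 5.2, so it is not part of this point.

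**Conclusion.** The point holds in a limited form. As written, a patient with an active electronic implant other than a pacemaker, sited outside the pelvis, meets all criteria and would lie over the field generator. No section of the protocol closes this gap. That the pacemaker bullet is aimed at interference with active electronics is an inference from the structure of section 4.3, not a statement in the protocol. The size of any hazard is not documented.

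At assumed prevalences of 0.5% to 2%, the chance of enrolling at least one carrier among the 20 extension patients is about 10% to 33%, if all 20 reach the generator. This says nothing about the chance of harm. No endpoint, sample size or analysis figure is affected. The change is worth making because it bears on safety, which is part of the primary objective, and costs very little.

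**What to change.** 1. Reconcile section 4.3 with the risk assessment and electrical safety report promised in section 5.2, and state the reason for the pacemaker exclusion.
2. Unless the risk assessment documents that other active implants are safe in the field, extend the pacemaker bullet to active implanted electronic devices in general. If it does document this, say so in the protocol and cite it.
3. Name interference with active implants among the risk domains in section 5.2.

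The cost is one line in section 4.3, one in section 5.2 and a matching entry on the screening form. Under the assumed prevalences, the wider exclusion would remove an expected 20 × 0.005 = 0.1 to 20 × 0.02 = 0.4 of the 20 extension patients. These are averages, not upper limits.

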### **4.4 Sample size calculation**

This project is a proof of principle study. The goal is to assess feasibility and safety of the electromagnetic navigation system in a clinical environment during surgery. The system is already extensively tested in a non-clinical setting and has shown to be highly accurate. Pre-clinical tests within the OR have shown that some environmental changes might influence the accuracy of the system. However, assessing all combinations of possible environmental changes is impossible. We have to perform this registration study to have an estimate of the expected environmental influences during surgery.

During the course of the study, we have identified an import application for navigation; i.e. locally advanced T3 or T4 rectal tumour and tumour recurrences in the abdomen and pelvic area. Lately, due to logistic reasons (OR planning), the drop-out of patients who signed informed consent was higher than expected. In order to obtain sufficient accuracy measurements to obtain statistical relevant numbers in this study, 20 more patients should be included. This accounts for 15 successful measurements and 30% chance of failure.

---

Inclusion of maximally 95 patients will be sufficient to evaluate and improve the system during abdominal surgery. No sample size calculation is performed.

---

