## **8. STATISTICAL ANALYSIS**

### **8.1 Descriptive statistics**

In this registration study, distances will be measured between the estimated probe positions with respect to the bifurcation of the common iliac artery into the left and right artery, both bifurcations into the internal and external iliac artery and ureters. Measurements will be compared within patients to assess patient specific systematic errors, and between patients to assess system specific systematic errors. Due to the nature of a registration study, significance can not be estimated. However, usability and subjective assessment of experience by the surgeons will be valuable for future projects. Assessment of the ureter tracts will be based on the surgeon's opinion, and scored in terms of excellent, reasonable, dubious or wrong. Actual assessment of tumour boundaries and suspected lymph node locations will be recorded and cross-referenced with pathology

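### Section 4.4: 20 further patients at a 30% failure rate give 14 expected successful measurements, not the 15 stated

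*Protocol*

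**What the plan says.** Section 4.4 (Sample size calculation) explains that recruitment is being extended because, for logistic reasons, "the drop-out of patients who signed informed consent was higher than expected". It then sets the size of the extension: "In order to obtain sufficient accuracy measurements to obtain statistical relevant numbers in this study, 20 more patients should be included". The next sentence gives the yield: "This accounts for 15 successful measurements and 30% chance of failure".

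The section closes with the overall ceiling, "Inclusion of maximally 95 patients will be sufficient to evaluate and improve the system during abdominal surgery", and with the statement "No sample size calculation is performed". Section 8.1 (Descriptive statistics) adds that "Due to the nature of a registration study, significance can not be estimated".

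Section 4.4 gives no observed failure rate, no required probability of reaching 15, and no precision target.

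**The concern.** The section gives an enrolment figure, a failure rate and a yield. Any two of these fix the third, and the three printed do not agree. A reader who applies the stated failure rate to the stated enrolment does not get the stated yield.

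What is at stake is modest. This sentence is the numerical reasoning given for asking 20 more people to take part. According to the protocol summary, each participant has an additional contrast-enhanced CT scan, an intra-operative XperCT scan and up to 20 minutes of extra operating time. Whoever approves the extension should see the return that the stated assumptions actually give.

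**Working it through.** **Inputs, all from section 4.4**

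- Additional patients: n = 20
- Successful measurements aimed at: s = 15
- Chance of failure per patient: d = 0.30

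**Step 1. Reproduce the plan's figure.** Adding 30% to the target gives s x (1 + d) = 15 x 1.3 = 19.5, which rounds up to 20. This matches the protocol exactly and is the likely route, although the protocol does not show its calculation.

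**Step 2. Check that route.** It applies the 30% to the successes. A chance of failure applies to the patients enrolled, so the enrolment needed for an expected 15 successes is s / (1 - d) = 15 / 0.70 = 21.4, that is 22 patients. Those 22 would give 22 x 0.70 = 15.4 expected successes. The difference from the plan is 22 - 20 = 2 patients.

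**Step 3. Work forward from the plan's enrolment.** n x (1 - d) = 20 x 0.70 = 14 expected successes. The difference from the plan is 15 - 14 = 1 measurement.

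**Step 4. Find the failure rate that would make 20 and 15 agree.** 1 - 15/20 = 0.25. At a 25% failure rate, 20 x 0.75 = 15.

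| Failure rate | Patients | Expected successes |
|---|---|---|
| 30% (as stated) | 20 (as stated) | 14.0 |
| 30% (as stated) | 22 | 15.4 |
| 25% | 20 (as stated) | 15.0 |

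**Step 5. Illustration only.** Assume that patients fail independently of one another, each with the same probability. The number of successes is then binomial.

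- 20 patients, 30% failure: P(15 or more) = 0.416
- 22 patients, 30% failure: P(15 or more) = 0.671
- 20 patients, 25% failure: P(15 or more) = 0.617

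The protocol sets no required probability, so these values are not a test that the plan passes or fails.

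**The case against.** The strongest reply is that this is a planning approximation in a study that openly has no formal sample size. Section 4.4 calls the project a proof of principle study and says no calculation was done, and section 8.1 confines the analysis to description. Inflating by 1 + d instead of dividing by 1 - d is a common shortcut. Here it moves the answer by two patients, or one expected measurement, and nothing in the analysis turns on whether 14 or 15 measurements are obtained.

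Most of that stands, and it limits how much weight the point can bear. It does not make the sentence correct. Explaining how 20 was reached does not make 20 x 0.70 equal 15, and disclaiming a formal calculation does not excuse a wrong figure in the informal one.

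Three stronger readings are tempting, and the documents do not support them.

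- **That the extension will probably fail.** A reader might infer this from the 42% chance of 15 or more. The protocol uses 15 as a planning count and never as a threshold to be assured. Even the correctly inflated 22 patients reach it with only 67% probability. The 42% also assumes independent failures at exactly 30%. The drop-out is attributed to operating-room planning, which need not affect patients independently, and at a 25% rate the probability rises to 62%.
- **That the maximum of 95 is undermined.** The sentence concerns the 20-patient increment. It does not justify the remaining 95 - 20 = 75, and replacing 15 by 14 leaves the maximum where it is.
- **That the precision of the accuracy estimate can be calculated from 14 or 15 patients.** Section 4.4 refers to sufficient measurements in the study as a whole, and nothing says that the extension patients are analysed separately. Section 8.1 describes comparisons within and between patients. It defines no confidence interval for a mean error in the extension group.

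**Conclusion.** The point holds as a small arithmetic inconsistency. Under the protocol's own assumptions, the extension is expected to yield 14 successful measurements and not 15. The conclusion rests only on reading the 30% as the chance that an enrolled patient gives no successful measurement, which is its ordinary meaning. It does not depend on independence between patients or on any distribution.

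The size is one expected measurement out of 15 in the extension, equivalent to two patients if the original target were kept at 30% failure. It is not a material sample-size error, because no hypothesis test, stopping rule or stated conclusion depends on the figure.

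**What to change.** Keep the 20 additional patients and the maximum of 95, and correct the sentence on yield in section 4.4. There are two ways to do so, depending on what the study has observed.

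- If 30% is the right failure rate, state that about 14 successful measurements are expected from the 20 additional patients at a 30% failure rate.
- If the failure rate seen so far is really 25%, replace 30% by 25% and keep 15.

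The investigators should choose by looking at their own record of failures, which section 4.4 does not report. If they wish to add the 42% chance of 15 or more, it should be labelled as an illustration that assumes independent failures at exactly 30%.

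The cost is one sentence. No patients are added, and no procedure or analysis changes. Under the first option, the stated yield becomes lower by one.

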## 5. TREATMENT OF SUBJECTS

### 5.1 Study procedure

All included patients are already scheduled for surgery. The programmed surgical procedure will not in any way be influenced by the measurements, other than an extension of total operating time by a maximum of 20 minutes, which is clinically acceptable in surgical procedures which generally take over 3 hours.

Specific study procedure:

